### Statistical analyses

#### Quantitative measures

Prior to the analysis, data will be checked for missing values, outliers, and normality. Possible differences between the study groups’ baseline characteristics will be tested with *t* tests for continuous variables and χ^2^ tests for categorical variables. In case of missing data, we intend to test if data is missing completely at random (MCAR) based on a comparison of the baseline characteristics of study completers and participants with missing values. If *p* <0.05 for (one of) the variables in the model, the missing values are non-random. In case of data MCAR, the specification of a missing value or dropout model is not necessary and list-wise deletion will be applied. In case of missing data not at random, we will apply a multiple imputation-based strategy [56].

To examine differences in the outcomes of the intervention and the waiting-list control groups during the intervention period, an analysis of covariance (ANCOVA) will be conducted with post-intervention outcome as the dependent variable, intervention (“Partner in Balance,” waiting-list control group) as the between-subjects variable and the pre-intervention outcome, emotional instability, quality of the relationship, educational level and relationship to the care recipient as covariates. Each outcome will be assessed as a dependent variable. Group differences in the post-intervention outcome adjusted for its baseline value will be examined to test the primary hypothesis. If differences are found, the inter-group effect size will be calculated according to Cohen’s *d*.

To analyze changes in the primary and secondary outcomes during the total study period, the data from the intervention-only group and the waiting-list group receiving the intervention after 8 weeks will be combined using a linear mixed model (LMM). The LMM will estimate fixed effects (regression slopes) for the change during the waiting-list interval (T0–T1 as measured in the waiting-list group only) and fixed effects for change in the intervals during (T1–T2) and after (T2–T3, T3–T4, T4–T5) the intervention period (measured in the waiting-list group after the first 8 weeks and in the intervention group). This will allow us to compare the rate of change in those receiving no intervention (T0–T1) with those receiving the intervention (T1–T5) while accounting for the fact that data are nested in individuals and, therefore, correlated. Intervals will be entered as a categorical variable (five levels) using dummies. Model fit of models with random intercepts (at the participant level) and models with random intercepts and random slopes (at the interval level) will be compared using likelihood ratio tests.

Emotional instability and quality of the relationship will be included as covariates because they are expected to influence the difference between groups. Coach will be introduced into the analysis as a random factor to estimate the variability attributable to the coach. For goal attainment, descriptive statistics will be used to calculate the total number of goals set per domain. Mean goal attainment scaling scores (*T*-scores) will be calculated with a standard formula [38] for each measurement time point.

All analyses will be carried out according to the intention-to-treat principle using IBM SPSS statistics 22.0 for Macintosh. All tests of significance will report mean change and will be two-tailed, with α set at 0.05.

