### Sample size

We determined our sample size based on previous online intervention studies on caregivers of people with dementia using the CSES as outcome measure, the use of repeated measures, within-between interaction with a mean effect size of 0.2 [55], the following assumptions: alpha 0.05, power 85 % and 25 % loss to follow-up. In accordance with these criteria, we aim to enroll 80 participants (40 participants per group).

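### A low-powered baseline comparison decides how missing data are handled: a non-significant result leads to list-wise deletion despite intention-to-treat, and a significant one is mislabelled as not at random

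*Protocol article*

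**What the plan says.** All of this is in the protocol article, under Statistical analyses, Quantitative measures, except the loss figure.

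- The test: "we intend to test if data is missing completely at random (MCAR) based on a comparison of the baseline characteristics of study completers" and of participants with missing values.
- The trigger: if p < 0.05 "for (one of) the variables in the model, the missing values are non-random".
- Otherwise: "In case of data MCAR, the specification of a missing value or dropout model is not necessary and list-wise deletion will be applied".
- After a significant result: "In case of missing data not at random, we will apply a multiple imputation-based strategy". A reference is cited, but no imputation model is described. There is no missing-at-random category.
- The analysis principle, later in the same section: "All analyses will be carried out according to the intention-to-treat principle".
- The Sample size section assumes "alpha 0.05, power 85 % and 25 % loss to follow-up" and does not say at which visit the loss is counted.

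The primary hypothesis is tested by an ANCOVA of the post-intervention (T1) outcome. It adjusts for the baseline outcome, emotional instability, relationship quality, education and relationship to the care recipient. A linear mixed model then covers the whole study period.

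**The concern.** The rule has four faults.

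1. It treats failure to reject as proof. MCAR is the null hypothesis, and a small comparison often fails to reject a false null.
2. It looks only at baseline. Caregivers who stop because the programme is not helping them may look like everyone else at baseline.
3. Its labels are wrong. A baseline difference shows that missingness is related to something observed, which is compatible with MAR. The article calls this not at random and responds with multiple imputation, which in its usual form assumes MAR.
4. The list-wise branch removes randomised participants from analyses that the same section calls intention-to-treat.

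At stake is who enters the primary analysis of an 80-person trial that plans to lose a quarter of them. If deletion covers everyone who does not complete the study, it would also remove T1 scores already collected from people who leave later, and visits that the mixed model could use.

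**Working it through.** **Plan's own figure.** Inputs from Sample size: effect size 0.2 (read as Cohen's f), alpha 0.05, power 85%, 25% loss. Assumed because not stated: 2 measurements, correlation 0.5. For the within-between interaction, noncentrality = f² × N × m / (1 − ρ) = 0.04 × 60 × 2 / 0.5 = 9.6 on 1 and 58 degrees of freedom, which gives power 0.861. Then 60 / 0.75 = 80, the stated total. So 25% loss means about 60 with complete data and 20 without.

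**Power of the deciding test.** Two-sample t test, two-sided 0.05, 78 degrees of freedom, noncentrality = d × √(n₁n₂ / (n₁ + n₂)). With 60 and 20, √(1200 / 80) = 3.873. For d = 0.3 the noncentrality is 1.16, and for d = 0.5 it is 1.94; the critical value is 1.99. The visit for the 25% is not stated, so smaller losses are shown too.

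| Participants with missing data (of 80) | Power at 0.3 SD | Power at 0.5 SD |
|---|---|---|
| 20 | 21% | 48% |
| 12 | 16% | 35% |
| 8 | 12% | 26% |

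With less loss, fewer people are affected but the test is weaker still.

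**The opposite error.** Under true MCAR the chance that at least one of k independent variables has p < 0.05 is 1 − 0.95^k: 23% for k = 5 and 40% for k = 10. The article does not give the number of variables.

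**What the test can and cannot see.** Simulated trials: 40 per arm, about 25% missing, five independent baseline variables including the baseline outcome, baseline–T1 correlation 0.5. These mechanisms are assumed and illustrative.

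| Dropout mechanism | Rule declares MCAR | List-wise ANCOVA |
|---|---|---|
| True MCAR | 78% | bias about 0.00 SD |
| Driven by baseline outcome, log odds 0.8 per SD | 15% | bias about 0.00 SD |
| Active arm only, driven by poor T1 outcome, log odds 0.8 per SD | 73% | true 0.30 SD estimated as 0.44 SD |

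The rule reacts to the mechanism that the ANCOVA already handles. It hardly separates response-driven dropout (73%) from true MCAR (78%). The last row depends on its assumptions: at log odds 0.4 the estimate is 0.38 SD, and with the same dependence in both arms it is 0.28 SD.

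**What using all observed data changes.** There are two cases under the mechanism of the last row.

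- The T1 score itself is missing: list-wise ANCOVA gives 0.44, and multiple imputation under MAR by arm also gives 0.44. Imputation does not remove this bias.
- The participant leaves after T1, so the T1 score is observed: an ANCOVA on all T1 data gives 0.30. Deleting all study non-completers gives 0.44.

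**Intention-to-treat.** Under the MCAR branch, 80 − 0.25 × 80 = 60 of 80 randomised participants would remain if the 25% applied to the analysis concerned.

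**The case against.** The case on the other side is substantial, and much of it stands.

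- The ANCOVA adjusts for the baseline outcome and four other baseline variables. If dropout depends only on these, list-wise deletion is approximately unbiased and either branch gives nearly the same estimate. A reader might infer that the primary analysis is invalid whenever data are missing; the documents do not support that.
- A reader might also take the rise from 0.30 to about 0.45 SD as bias that the main repair would remove. It comes from an assumed MNAR mechanism, and MAR imputation shares it when T1 is missing.
- False rejection of MCAR only sends the analysis to imputation, which is valid under MCAR. That error does little harm.
- The article does not say which kind of multiple imputation is meant, and the cited source is not at hand. An MNAR-type method cannot be excluded, although none is described.
- The article does not say outright that the mixed model loses participants with a missing visit. It does not exempt that model either, so the loss of visits is conditional.
- The rule is fixed in advance and uses no treatment effects, so it offers no obvious way to pick a favourable result.

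What does not stand is a defence that these are details left to a fuller plan. The article states the rule completely: test, threshold and both consequences.

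**Conclusion.** Wrong as written. A test with 21% to 48% power per variable for differences of 0.3 to 0.5 SD, at an assumed 60 versus 20 split, cannot establish MCAR, and no baseline test can detect dropout that follows response. The significant branch carries the wrong label, and the non-significant branch conflicts with the intention-to-treat statement.

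The size of any bias in the primary estimate cannot be read from the documents. It is about nil if dropout depends only on the ANCOVA covariates. It could be material if list-wise deletion extends to all study non-completers and late dropout follows a poor T1 response: 0.44 against a true 0.30 SD in the illustration, where keeping all T1 data gives 0.30. When T1 itself is missing for reasons tied to its value, no MAR method cures the bias, and only a sensitivity analysis can show how much it matters.

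**What to change.** 1. Remove the MCAR test as a decision rule, and remove list-wise deletion. Keep the completer comparison as description only.
2. Fix one primary approach in advance for all randomised participants and all observed data. For the T1 ANCOVA, use multiple imputation under MAR, done by arm, with the ANCOVA covariates and the available visit outcomes in the imputation model. For the mixed model, use likelihood estimation on every observed visit.
3. Correct the wording: a baseline difference indicates missingness related to observed data, compatible with MAR; MNAR is a separate assumption that these data cannot test.
4. Add one delta-adjusted imputation, in which participants with missing outcomes do worse than MAR predicts, as the MNAR sensitivity analysis.

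The cost is a rewritten paragraph, a routine imputation run and one sensitivity analysis. Sample size and data collection do not change.

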**Methods/design:**

A mixed-method, single-blind, randomized controlled trial with 80 family caregivers of community-dwelling people with (very) mild dementia will be conducted. Participants will be randomly assigned to either the 8-week blended care self-management program “Partner in Balance” or a waiting-list control group. Data will be collected pre intervention and post intervention and at 3-, 6- and 12-month follow-ups. Semi-structured interviews will be conducted post intervention. A process evaluation will investigate the internal and external validity of the intervention. Primary outcomes will include self-efficacy and symptoms of depression. Secondary outcomes will include goal attainment, mastery, psychological complaints (feelings of anxiety and perceived stress), and quality of life. Possible modifying variables such as caregiver characteristics (quality of the relationship, neurotic personality) and interventional aspects (coach) on the intervention effect will also be evaluated. A cost-consequence analysis will describe the costs and health outcomes.

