#### The personal coach

The personal coach is an experienced professional (psychologist or psychiatric nurse) from one of the participating sites. Coaches will receive a 1-day training on self-management techniques and online help before the start of the intervention. They will receive supervision from an experienced professional in the fields of psychology and self-management to ensure high-quality feedback.

Coaches support participants in choosing modules that fit their situation, help identify feasible goals, offer techniques to achieve goals and provide general constructive feedback on their assignments. Coaches will be matched with the participants assigned to them via a personal login code.

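### The primary T1 ANCOVA names no coach term although only the intervention arm has coaches by then; the plan should state whether and how coach enters that model

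*Protocol article*

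**What the plan says.** All references are to the protocol article.

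- **Primary test** (Statistical analyses, Quantitative measures). For the T1 comparison, "an analysis of covariance (ANCOVA) will be conducted with post-intervention outcome as the dependent variable". Arm is the between-subjects variable, with "the pre-intervention outcome, emotional instability, quality of the relationship, educational level and relationship to the care recipient as covariates". Its role is explicit: "Group differences in the post-intervention outcome adjusted for its baseline value will be examined to test the primary hypothesis".
- **Long-term model** (same section). A linear mixed model combines both groups over the whole study. The dependence it names is that of repeated measurements, "accounting for the fact that data are nested in individuals and, therefore, correlated".
- **Coach term** (same section, in a separate paragraph after the mixed model). "Coach will be introduced into the analysis as a random factor to estimate the variability attributable to the coach". No model is named.
- **Coaches** (The personal coach). "The personal coach is an experienced professional (psychologist or psychiatric nurse) from one of the participating sites". They help choose modules and goals and give feedback. "Coaches will be matched with the participants assigned to them via a personal login code".
- **Controls** (Control group). They wait 8 weeks and receive the programme only after the post-test.
- **Stated interest in coach** (Abstract, Methods/design). The influence of "interventional aspects (coach) on the intervention effect will also be evaluated".
- **Sample size.** 80 participants, 40 per group. Coach clustering is not mentioned.

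**The concern.** Participants guided by the same coach may have similar outcomes. At T1 this similarity can arise in one arm only, because controls have not yet started. An ANCOVA without a coach term treats the intervention participants as independent. If the within-coach correlation is positive, it understates the variance of the intervention mean, and hence the standard error of the arm difference.

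At stake are the p-values and confidence intervals for the two primary outcomes, self-efficacy and depressive symptoms. Any error makes the evidence look stronger than it is.

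The sentence that adds coach does not settle this. If it refers to the mixed model only, the primary test ignores coach. If it also covers the ANCOVA, the form of the term matters, because half of the sample has no coach at that time.

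**Working it through.** **1. The plan's own figure.** The stated inputs are effect size 0.2, alpha 0.05, power 85% and 25% loss. I take 0.2 as Cohen's f and assume two measurements with correlation 0.5; the article does not state these three settings. The within-between interaction test then has noncentrality λ = f² × N × 2/(1 − ρ) with 1 and N − 2 degrees of freedom.

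- At N = 60, λ = 0.04 × 60 × 2/0.5 = 9.6 and power is 0.861.
- Allowing for dropout, 60/0.75 = 80.

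The stated 80 is reproduced with no allowance for coach.

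**2. Clustering in one arm.** Let n be the number analysed per arm, K the number of coaches and m = n/K the caseload, taken as equal. The ICC is that of the covariate-adjusted outcome within coach.

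- Design effect in the intervention arm: 1 + (m − 1) × ICC. In the waiting-list arm it is 1.
- Ratio of true to reported variance of the difference: R = (1 + [1 + (m − 1) × ICC])/2.
- Actual two-sided type I error: 2 × (1 − Φ(1.96/√R)).

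**3. Assumed inputs.** The article gives no K, caseload or ICC. I use K from 5 to 15, ICC from 0.01 to 0.10, and n = 30 (after the planned 25% loss) or n = 40 (no loss).

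**4. Worked cases at ICC 0.10 with 5 coaches.**

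- n = 30, m = 6: R = (1 + 1.50)/2 = 1.25, √R = 1.118, type I error 8.0%.
- n = 40, m = 8: R = (1 + 1.70)/2 = 1.35, √R = 1.162, type I error 9.2%.

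**5. Grid at 30 per arm.**

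| Coaches | ICC 0.01 | ICC 0.05 | ICC 0.10 |
|---|---|---|---|
| 5 | 5.3% | 6.5% | 8.0% |
| 10 | 5.1% | 5.6% | 6.2% |
| 15 | 5.1% | 5.3% | 5.6% |

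Simulation of a five-covariate ANCOVA (8000 runs per cell) gave 4.9% to 7.6% over the same range. At 40 per arm the formula gives 5.1% to 9.2%. The true standard error exceeds the reported one by 0.2% to 12% at 30 per arm, and by up to 16% at 40. With ICC 0, or one participant per coach, the type I error is exactly 5.0%.

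**6. Does the form of the coach term matter?** A null simulation used 40 per arm, 5 coaches and ICC 0.10 (2000 runs, coach variance in the treated arm only). Type I error was:

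- no coach term: 8.5%;
- one coach intercept shared by both arms, with controls linked to their later coach: 9.0%;
- waiting list coded as one extra coach level: 3.9%;
- coach effect on treated participants only: 5.8%.

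All three coded versions fit the words random factor, but they behave differently. The shared intercept does not remove the inflation; the treated-only term largely does.

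**7. Power.** Dividing λ by R at 60 completers lowers power from 0.861 to between 0.778 (5 coaches, ICC 0.10) and 0.860 (15 coaches, ICC 0.01). Keeping the planned power would need 60 × R completers: 75/0.75 = 100 enrolled at the upper end. At the lower end, 60.3 rounds up to 61, and 61/0.75 rounds up to 82.

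**The case against.** The strongest reply is that coach is already in the plan. The sentence adding it names no model and stands outside the mixed-model paragraph. It follows a sentence about emotional instability and relationship quality, which are both ANCOVA covariates and are tied there to the group difference. The paragraph can fairly be read as covering both models. This stands: a reader might infer that the plan treats all participants as independent, but the text supports only that the primary model is listed without coach and the coach sentence is not tied to it.

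Second, the inflation is conditional. It needs a positive ICC and several participants per coach, and neither is quantified. Contact consists of an intake, online feedback and an evaluation session, so the ICC may be small. The 9.2% figure needs 5 coaches and no attrition, whereas the plan expects 25% loss. This also stands, which is why the result is given as a range starting near 5%.

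Third, a reader might infer that the coach factor will estimate the wrong variance component, mixing in differences between caseloads and sites. The article does not say how the factor is coded, and the abstract's aim is compatible with a coach effect that acts only under treatment. That charge is not supported.

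Fourth, the exact random-effects structure is normally left to an analysis plan, which is not shown. That is true of the detail. But the article does set out the primary model by its terms and adds a coach factor elsewhere, and how the two fit together is open on the page.

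**Conclusion.** The point holds as a conditional one. The primary T1 ANCOVA is listed without coach, coaches act in one arm only before T1, the sponsor expects coach variability, and the coach factor is not assigned to a model.

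If the ANCOVA is run as listed, its type I error is about 5.1% to 8.0% at 30 per arm and at most about 9.2% at 40 per arm. This rests on the assumed 5 to 15 coaches, ICC 0.01 to 0.10 and equal caseloads. At ICC 0.01 it is 5.1% to 5.4%, which is negligible.

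The documents do not support the flat statement that the type I error exceeds 5% or that the primary result will be too optimistic. They show that it could be. The change is worth making because it is cheap and bears on the primary test.

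**What to change.** State that the primary T1 comparison is a partially nested mixed ANCOVA. Keep the listed fixed terms and add a random coach effect multiplied by an indicator for the intervention arm, so that it is zero for waiting-list participants. Use Satterthwaite degrees of freedom. Do not use a coach intercept shared across arms.

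In the long-term mixed model, let the coach effect act only on records after that person's programme has started. For the waiting-list group this means after T1.

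The cost is one extra random term in software already planned. Coach assignment exists through the login codes, but the article does not say that it is an analysis variable, so it must be carried into the dataset. The interval will be slightly wider, and with few coaches the coach variance will be imprecisely estimated.

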## Background

Family caregivers are currently becoming the main source of care for people with dementia [1]. However, dementia caregivers are at risk for depression, anxiety and other health problems [2]. Interventions aimed at reducing their burden of care might reduce dementia care costs in the long term if institutionalization can be postponed [3].

Many face-to-face caregiver support interventions have proven to be effective on caregiver distress (random effect size = 0.3), caregiver knowledge (random effect size = 0.5) [4], and self-efficacy (effect sizes ranging from 0.3 to 0.9) [5], but the expected future increase in the number of people with dementia raises concerns about whether care professionals can cope with this demand [6]. E-health interventions could serve as cost-effective alternatives for dementia caregiver support [7–9], both increasing caregivers’ access to support and extending the reach of such support [10–13]. The benefits of e-health are becoming increasingly recognized, and remote support for dementia caregivers is growing [14–16].

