Previous e-health studies on dementia caregivers show positive effects on caregiver confidence, stress, depression, and self-efficacy with effect sizes ranging from 0.2 to 0.3 [17]. Provision of tailored information, a coach, and the opportunity to interact with other caregivers shows the most promise [17]. Blending face-to-face guidance with online modules increases caregivers’ connection with the therapist and adherence [18, 19]. However, research on the effects of e-health on dementia caregivers lacks methodological rigor [17], and adverse effects of caregiving are often addressed in the later stages of dementia, when caregivers already feel overburdened [20]. Despite their low levels of life satisfaction and high levels of overload, caregivers do not use services in the early stages because they do not feel the need for such services or because they struggle with acceptance due their experience of stigma [20–22]. Supporting caregivers in the early stages of dementia could prevent high levels of burden and psychological problems in them in the later stages and delay institutionalization [23–26]. However, early-stage dementia caregiver support can be experienced adversely if the care does not suit the caregiver’s personal situation or the stage of the disease. Negative and stigmatizing information can make it difficult for caregivers to identify with and may hamper acceptance [20]. Learning to positively manage life with dementia, instead of managing the dementia itself in a self-management program, could facilitate caregivers’ adaptation to their new caregiving role. A focus on enhancing positive, intact experiences that are tailored to the individual caregiver’s situation may be more effective in increasing caregiver self-efficacy and reducing the negative consequences of caregiving at the later stages [20].

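### Cohen's d is to be calculated only where a difference is found, so the reported standardised effects would be selected on significance and exaggerated on average if true effects are small

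*Protocol article*

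**What the plan says.** The relevant text is in the protocol article, under Statistical analyses, Quantitative measures, and under Sample size.

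- Outcomes are compared at the end of the intervention period by ANCOVA. The post-intervention score is the dependent variable. The baseline score and four further variables are covariates. Every outcome is analysed this way, and the baseline-adjusted group difference tests the primary hypothesis.
- The effect size is conditional: "If differences are found, the inter-group effect size will be calculated according to" Cohen's d.
- Tests "will be two-tailed, with α set at 0.05".
- One quantity is promised without a condition: "All tests of significance will report mean change".
- The sample size rests on a "within-between interaction with a mean effect size of 0.2", with "alpha 0.05, power 85 % and 25 % loss to follow-up", and the result is that "we aim to enroll 80 participants (40 participants per group"). The metric of the 0.2 is not named.
- The Background reports that earlier e-health studies showed "positive effects on caregiver confidence, stress, depression, and self-efficacy with effect sizes ranging from 0.2 to 0.3". For face-to-face support it gives "self-efficacy (effect sizes ranging from 0.3 to 0.9").

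**The concern.** Some numerical difference between arms is always observed, so the condition only has a meaning if a found difference is a significant one. The article does not use that word, but with alpha fixed it is the workable reading. The condition then acts outcome by outcome, on the primary and the secondary outcomes alike.

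An estimate that is shown only when it is significant is biased away from zero, and the bias grows as power falls. The article argues from effect sizes of earlier studies, and its own d values are likely to be used in the same way. If those values exist only for outcomes that passed the test, a reader sees the favourable end of the results on the standardised scale and nothing comparable for the rest.

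The promise of mean change does not close the gap. Change within or between arms is not the difference adjusted for baseline, emotional instability, relationship quality, education and relationship to the care recipient, which is what the ANCOVA estimates.

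**Working it through.** **1. The plan's own figure.** The stated 80 can be reproduced if 0.2 is Cohen's f for a group-by-time interaction with 2 groups, m = 2 time points and a correlation ρ = 0.5 between them (m and ρ are assumptions).

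- Noncentrality: λ = f² × N × m / (1 − ρ) = 0.04 × 60 × 2 / 0.5 = 9.6.
- With 1 and 58 degrees of freedom the power is 86.1%. At N = 58 it is 84.9%, so 60 is the smallest even total that reaches 85%.
- 60 / (1 − 0.25) = 80.

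This f corresponds to a difference in change of 4f = 0.8 SD. Check: 0.8² / [2(1 − 0.5) × 4/60] = 0.64 / 0.0667 = 9.6. If 0.2 were Cohen's d in a plain two-group comparison, 85% power would need 2 × (1.960 + 1.036)² / 0.2² ≈ 449 per arm, so that reading does not give 80.

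**2. Inputs for the selection effect.**

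- From the article: two-sided alpha 0.05, 40 enrolled per arm, 25% loss, effects of 0.2 to 0.3 in earlier e-health studies.
- Assumed: 30 analysed per arm (40 × 0.75) up to 40 (no loss at 8 weeks); baseline-outcome correlation r of 0, 0.5 or 0.7; only the baseline score counted as a covariate in the degrees of freedom; the 0.2 to 0.3 read as SD units.

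**3. Formulas.** In SD units:

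- SE = √(1 − r²) × √(2/n)
- smallest significant estimate c = t(0.975; 2n − 3) × SE
- a = (c − d)/SE and b = (c + d)/SE
- probability of significance P = [1 − Φ(a)] + [1 − Φ(b)]
- mean significant estimate = d + SE × [φ(a) − φ(b)] / P

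**4. One case in full: n = 30, r = 0.5, d = 0.2.**

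- SE = √0.75 × √(2/30) = 0.2236
- c = 2.0025 × 0.2236 = 0.448
- a = 1.108, b = 2.897, P = 0.136
- mean = 0.2 + 0.2236 × (0.2159 − 0.0060)/0.1358 = 0.546
- ratio to the truth = 0.546 / 0.2 = 2.7

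With d = 0.3 the mean is 0.580 and the ratio is 1.9.

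**5. All cases** (mean significant estimate divided by the true effect):

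| n per arm | r | smallest significant estimate (SD) | d = 0.2 | d = 0.3 | d = 0.8 |
|---|---|---|---|---|---|
| 30 | 0 | 0.517 | 3.06 | 2.19 | 1.08 |
| 30 | 0.5 | 0.448 | 2.73 | 1.93 | 1.03 |
| 30 | 0.7 | 0.369 | 2.32 | 1.65 | 1.01 |
| 40 | 0 | 0.445 | 2.72 | 1.93 | 1.03 |
| 40 | 0.5 | 0.386 | 2.41 | 1.71 | 1.01 |
| 40 | 0.7 | 0.318 | 2.04 | 1.46 | 1.00 |

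A simulation that also lets the standard error vary gives nearly the same: 2.0 to 3.0 at d = 0.2, 1.5 to 2.15 at d = 0.3, and at most 1.08 at d = 0.8. At d = 0.4 it gives 1.2 to 1.7.

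**The case against.** Four points can fairly be made against this.

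- **The size depends on effects that the article does not fix.** A reader might infer that the published effects will be inflated two- to three-fold at the effects the trial expects. The documents do not support that. The 0.2 to 0.3 describes earlier e-health studies, the face-to-face range for self-efficacy reaches 0.9, and this programme is a blend of both. The planning value reproduces the sample size as an f, where exaggeration is at most 8%. Even at 0.3 SD the factor is below two in all but one case tried. This stands, and it is why the size is given as a range with its conditions. It does not show that 0.8 SD is the true effect, and the e-health figures cover domains measured here.
- **The number analysed at T1 is uncertain.** The 25% loss has no time point, follow-up runs to 12 months, and imputation is planned when data are not missing completely at random. This also stands, so 40 per arm is included.
- **Other results are not withheld.** A reader might infer that later reviews could not use the non-significant outcomes. That does not follow. Mean change is promised for every test, and nothing in the article says that means, SDs or intervals will be left out. A review could compute d from them. The harm is limited to the standardised adjusted effects that the trial itself reports.
- **Intervals and the choice of SD are details an article commonly leaves to a fuller document.** Agreed; their absence is not the point. The point is the condition, which is stated.

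**Conclusion.** The point holds as a reporting rule that is fixed badly. Whatever the true effect, making d depend on a found difference selects the reported values on the result, and mean change is not a substitute for the adjusted difference.

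The average exaggeration of the reported d is about 1.5- to 3-fold if true effects are 0.2 to 0.3 SD (2.0 to 3.1 at 0.2, 1.5 to 2.2 at 0.3), and under 10% if the true effect is about 0.8 SD. These figures rest on 30 to 40 analysed per arm, a baseline-outcome correlation of 0 to 0.7, and reading the condition as significance at two-sided 0.05. The degrees of freedom used by the extra covariates and the small-sample bias of d were ignored; both are minor.

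No test, error rate or primary conclusion is affected. The change should be made because it removes a known bias at no cost, but it does not threaten the trial.

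**What to change.** Delete the condition on Cohen's d. State instead that, for every primary and secondary outcome analysed by ANCOVA and whatever its p-value, the report will give the adjusted between-arm difference at T1 with its 95% confidence interval and the corresponding d. Name the standardiser, for example the pooled baseline SD. Mean change can stay as a descriptive addition.

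Reporting d for all outcomes removes the selection on significance. The cost is a change of wording: the ANCOVA already yields the adjusted difference and its standard error, and no test, sample size or data collection changes.
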